### Description of Primary Measures

#### Morisky Medication Adherence Scale (MMAS-4)

The MMAS-4 is a self-report scale for identifying medication non-adherence [35] and has been used in PD [16,41]. The scale is constructed of four items answered by 'yes' or 'no'. Four 'no' responses signifies perfect adherence. Any 'yes' responses indicates some degree of non-adherence with medication. We aim to recruit people scoring two or more 'yes' responses.

#### Parkinson's Disease Questionnaire - 39 (PDQ-39)

The PDQ-39 is a PD-specific QoL questionnaire. The scale has been extensively tested for reliability and validity and is widely used in both research and clinical practice [42,43]. Items making up the scale measure eight dimensions of health which are related specifically to PD: mobility, ADL, emotional wellbeing, stigma, social support, cognition, communication and bodily discomfort.

### Description of Secondary Measures

#### Movement Disorder Society - Unified Parkinson's Disease Rating Scale (MDS-UPDRS)

The MDS-UPDRS is a revised version of the Unified Parkinson's Disease Rating Scale [37,44]. The MDS-UPDRS has four parts of which we will use three, namely, (I) Non-motor Experiences of Daily Living; (II) Motor Experiences of Daily Living; (IV) Motor Complications. This represents 32 items from the scale. Twenty questions are completed by the patient/caregiver as part of a questionnaire and 12 questions are completed by the assessor through a structured interview format - 6 items in part I and IV, respectively. When tested for its clinimetric properties, the scale has been shown to have high internal consistency, reliability and validity, and correlates well with the original UPDRS [44]. Competency based training and an online examination developed by the Movement Disorders Society have been completed by the Chief Investigator.

#### Beliefs about Medication Questionnaire (BMQ)

The BMQ is comprised of two scales: (1) an 11 item questionnaire relating to prescribed medication, (2) an 8 item questionnaire relating to general views about taking medication. The questionnaires assess beliefs about the necessity of prescribed medication for controlling illness and concerns about taking medications [38]. Respondents rate each item on a five point Likert-type scale depending on their degree of agreement (1 strongly disagree, 5 strongly agree). Higher scores indicate higher levels of concern or strong beliefs towards the use of medication.

#### EuroQoL (EQ-5D)

The EQ-5D is an established, standardised generic health utility index tool used extensively in clinical studies [39]. It consists of five items covering mobility, self-care, usual activity, pain/discomfort, and anxiety/depression domains. A visual analogue scale represents one final characteristic of the instrument. It provides a simple descriptive profile and can be used to estimate a single index value for a respondent's health status and change in Quality Adjusted Life Years (QALYs).

#### Caregiving Distress Scale (CDS)

The CDS is a concise measure designed to assess and profile informal caregivers with respect to stressful outcomes. The scale was developed in a PD population from various caregiving measures including a wide range of items and varying associations with distress [28,40]. The CDS comprises five distinct dimensions comprising 17 items that have a potential negative impact on caregivers. Answers are provided on a 0-4 scale based on level of agreement.

#### Satisfaction Questionnaire

To investigate patient and spouse/carer satisfaction with the CAAT-PARK process, we will post out a satisfaction questionnaire with the follow-up (week 12) outcome measures.

### Description of Other Measures (Prognostic Factors)

#### Montreal Cognitive Assessment Scale (MoCA)

The MoCA is a 30-point scale delivered by a rater. The MoCA covers a range of executive functions and has been proposed to be the most appropriate scale for assessing cognitive impairment in PD research where cognition is not the primary outcome [45]. The MoCA has six orientation questions and a five word memory recall task. A clock drawing task and a cube copy test assess visuospatial function. Attention/concentration is assessed using serial 7's, target mapping and digit span forward and backwards tasks. Executive functions are evaluated using a shortened version of the Trial Making B Test, phonemic fluency, and a verbal abstraction task.

#### Hospital Anxiety and Depression Scale (HADS)

The HADS is a self screening questionnaire for anxiety and depression [46]. The HADS consists of 14 questions, seven for each anxiety and depression and has been widely used and validated [47].

In addition to levels of anxiety/depression and cognitive capacity, we will identify and present demographics at baseline: participants' age, duration and severity of PD (Hoehn & Yahr score), medication profile (type of medications, dosage level and frequency), socioeconomic status, co-morbidities, level of education and whether medication is self-administered or given by a spouse/carer.

### Follow-up Measurements

Baseline measures assessed to determine the efficacy of CAAT-PARK will be repeated immediately post intervention and at 12-weeks post randomisation (follow-up) (Figure 2). For the control group receiving TAU, assessments will be at week seven and week twelve. For the CAAT-PARK group, post intervention assessments will be at week seven or eight and then at week 12. This additional week at the midway post intervention time point accommodates potential sickness or time away providing flexibility from a pragmatic perspective.

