**Methods/Design:**

A parallel, randomised controlled trial will be conducted to investigate whether carer assisted adherence therapy is effective for improving medication adherence and quality of life. We aim to recruit 40 patient/carer pairs into each group. Participants will be randomly assigned by the Clinical Research Trials Unit at the University of East Anglia. Adherence therapy is a brief cognitive-behavioural approach aimed at facilitating a process of shared decision making. The central theory is that when patients make shared choices with a professional they are more likely to continue with those choices because they are personally owned and meaningful. Outcomes will be rates of adherence and quality of life, determined by the Morisky Medication Adherence Scale-4 and the Parkinson's disease Questionnaire-39 respectively. Assessments will take place post randomisation, immediately post intervention and 12-weeks post randomisation. Primary outcomes are adherence and quality of life at 12-week follow-up. Efficacy will be determined using intention-to-treat analysis. Independent samples t-tests will compare mean changes between groups from baseline to follow-up. Per protocol analysis will be conducted based on individuals with no major protocol deviation. Where imbalances in baseline characteristics are identified, an adjusted analysis will be performed using a regression model. Analysis will be masked to treatment allocation.

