## Methods/Design

### Trial Design

A parallel group, randomised controlled trial will be conducted to compare Carer Assisted Adherence Therapy (CAAT-PARK) with Treatment as Usual (TAU) for non-adherent people with PD and their spouse/carers. The study will compare the two groups immediately post intervention and at 12 weeks post randomisation (follow-up).

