**Figure 3 F3:**
[figure not shown]
**CAAT-PARK model**.

Participants allocated to CAAT-PARK will receive seven 30 minute sessions at weekly intervals. Assessment and problem solving will be delivered twice, making up seven sessions in total. Each weekly session will incorporate a separate theme, however, each session will be participant centred. Where a patient's carer has consented to the trial, the intervention will be delivered to the carer at the same time. Ten sessions over the course of the trial will be recorded to determine treatment fidelity against the CAAT-PARK manual [49].

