### Efficacy Analysis of Primary Outcomes

The efficacy of CAAT-PARK will be determined by comparing the mean change in values of the two groups from baseline to week 12 follow-up. Analysis between the two groups will be made using an independent sample *t*-test. Intention to treat (ITT) and per protocol (PP) analyses will be undertaken. For the intervention group, this is irrespective of their compliance with CAAT-PARK. ITT analysis will represent the primary analysis and will be used for evaluation of all outcomes. PP analysis will include patients who comply with the treatment as defined by completing five or more out of seven CAAT-PARK sessions. All participants will undergo sub-group analysis testing for potential effect modification for the presence of a spouse/carer on the treatment effect. Appropriate adjustments will be made in the statistical analyses for potential factors that are unevenly distributed between the groups. Specifically, participants with significantly high reported levels of cognitive impairment and anxiety and depression at baseline (assessed with the MoCA and HADS, respectively) will be analysed to determine the independent impact of these prognostic factors on the treatment effect. Adjusted estimates will be obtained by identifying baseline imbalances and incorporating these into a regression model using pre and post intervention primary outcome scores.

If normal distribution assumptions are not met, even after suitable transformations, non-parametric analysis will be adopted. Imputation for missing/incomplete data will be carried out using chained equations with all outcome measures and potentially correlated baseline values. A total of 10 imputed datasets will be created.

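### The post-intervention assessment may fall in week 7 or 8 for CAAT-PARK but only in week 7 for TAU, so the timing of this non-primary comparison depends on the arm

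*Protocol article*

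**What the plan says.** All the relevant text is in the protocol article.

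- **Follow-up Measurements, TAU:** "For the control group receiving TAU, assessments will be at week seven and week twelve".
- **Follow-up Measurements, CAAT-PARK:** "For the CAAT-PARK group, post intervention assessments will be at week seven or eight and then at week 12".
- **Follow-up Measurements, reason for the difference:** "This additional week at the midway post intervention time point accommodates potential sickness or time away providing flexibility from a pragmatic perspective".
- **Trial Design, use of the visit:** "The study will compare the two groups immediately post intervention and at 12 weeks post randomisation (follow-up". The mid-point is therefore a planned between-group comparison.
- **Abstract, primary time point:** "Primary outcomes are adherence and quality of life at 12-week follow-up". The Efficacy Analysis of Primary Outcomes section agrees, basing efficacy on "comparing the mean change in values of the two groups from baseline to week 12 follow-up".
- **Intervention section, length of therapy:** "Participants allocated to CAAT-PARK will receive seven 30 minute sessions at weekly intervals".

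Study Limitations adds that follow-up outcomes are not masked. The analysis section imputes missing data by chained equations that include all outcome measures.

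**The concern.** Illness and holidays are not consequences of allocation, yet only one arm is given time to work around them. A comparison at a nominal visit assumes that both arms are measured on the same clock. Here the clock can run a week longer in one arm, and allocation is known when the visit is deferred.

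Three things could follow, in decreasing order of certainty:

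1. Elapsed time from randomisation differs by arm. This follows directly from the text.
2. The chance of a missing mid-point visit may differ by arm, if a CAAT-PARK participant who is away in week 7 can be seen in week 8 and a TAU participant cannot.
3. Health on the day may differ by arm, if illness on the due date leads to deferral in CAAT-PARK only. PDQ-39, EQ-5D and MDS-UPDRS all measure health status, so this would tend to favour CAAT-PARK.

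What is at stake is the interpretation of the mid-point contrast. A larger sample would not remove a difference of this kind.

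**Working it through.** No figure stated in the article depends on this rule, so there is none to reproduce. The check is of the schedule, followed by an illustration of scale.

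**Step 1: the two schedules side by side.** Weeks are taken as counted from randomisation. The article says so for week 12, and week 7 is read the same way.

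| | TAU | CAAT-PARK |
|---|---|---|
| Mid-point visit | week 7 | week 7 or 8 |
| Interval to week 12 | 12 − 7 = 5 weeks | 12 − 7 = 5 or 12 − 8 = 4 weeks |
| Final visit | week 12 | week 12 |

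The arms differ by up to 8 − 7 = 1 week at the mid-point and by 0 at week 12.

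**Step 2: what the extra week is for.** The article allows two readings.

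- *Slack for the assessment day.* The sentence giving the reason attaches the week to the mid-point visit itself. On this reading, a participant who is ill when the visit is due is seen a week later.
- *Slack for therapy.* Seven weekly sessions end in week 7. One missed week moves the end to 7 + 1 = week 8, and the assessment is meant to follow the end of therapy. On this reading, illness in any earlier week moves the visit, and the day itself need not be a healthier one.

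Unequal timing is present on both readings. The health-on-the-day effect belongs mainly to the first.

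**Step 3: illustration of scale.** Every rate and effect below is assumed. Only the SD of 8.89 and the planning difference of 6.13 PDQ-39 points come from the article (Sample Size).

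(a) Timing alone. Bias = share of CAAT-PARK visits moved × drift per week.

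- Low: 0.10 × 0.02 SD = 0.002 SD
- High: 0.50 × 0.10 SD = 0.05 SD

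(b) Sick-day deferral in one arm only. Bias = share ill when the visit is due × sick-day deficit.

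- Low: 0.05 × 0.25 SD = 0.0125 SD, and 0.0125 × 8.89 = 0.11 points
- High: 0.20 × 1.0 SD = 0.20 SD, and 0.20 × 8.89 = 1.78 points

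Case (b) is an upper bound in form. It supposes that every ill CAAT-PARK participant is deferred and fully recovered a week later, and that every ill TAU participant is assessed while ill.

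**Step 4: the primary time point.** The week 12 visit is the same in both arms, so the timing bias there is 0. An indirect route exists, because mid-point values may inform imputed week 12 values. It depends on arm-dependent missingness, which the article does not establish.

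**The case against.** The strongest defence is that the allowance serves therapy. TAU has no sessions to catch up, which would explain why only CAAT-PARK was given a second week. This stands as a plausible reading and removes most of the argument about health on the day. It does not remove the unequal timing: one arm's visit would follow completion of sessions while the other's follows the calendar.

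A second defence is that an article gives nominal weeks and leaves visit tolerances to the full protocol. The diagram of assessment time points was also not available to this review. That is fair as regards an ill TAU participant, whose handling is simply not stated. It does not answer a rule that the article does state, separately for each arm and with a reason common to both.

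A reader might go further and infer that the plan picks healthier assessment days for CAAT-PARK, with a bias equal to a sizeable share of the 6.13-point difference. The article does not support that:

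- Time away, the other stated reason, involves no sick-day effect.
- Sick-day bias and uneven missingness are largely alternatives. If ill TAU participants are missed, their poor scores are not observed; if they are assessed, they are not missing.
- The 6.13 points belong to the sample-size case for a primary outcome, whose primary time point is week 12. They are not a target for the mid-point.

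**Conclusion.** The point holds as a limited one. The article states an arm-dependent window for a visit at which it plans to compare the arms, and the reason given applies to both. Unequal timing of up to one week is certain as a possibility under the rule. Unequal missingness or unequal health on the day is possible but unsettled.

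The bias cannot be computed from the article. The illustrative ranges in the working suggest that it is probably small, and they rest wholly on assumed rates and effects. The primary week 12 comparison is not directly affected, and nothing here puts the trial's main conclusion in doubt. The change is worth making because the difference between arms is avoidable and cheap to remove.

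**What to change.** Replace the two arm-specific statements under Follow-up Measurements with one rule counted from randomisation, for example: *The post-intervention assessment takes place at week 7, or at week 8 if the participant is ill or away, in CAAT-PARK and TAU alike; the actual date of each assessment is recorded.* Make the visit schedule agree.

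A common window equalises what is permitted. If catching up sessions still moves some CAAT-PARK visits, the recorded dates will show how far the arms differ in practice.

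Two other remedies are not recommended. Fixing week 8 for everyone would put a delay between therapy and assessment for those who finish in week 7. Assessing before therapy has ended would change what the visit measures. Each is a trade-off, and neither is needed.

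The cost is a sentence and slightly more spread in TAU assessment times, with no added visits. Recruitment stood at 16% of target when the article was submitted, so at that stage most participants could still have been assessed under the common rule.

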**Figure 2 F2:**
[figure not shown]
**Study Design - assessment time points**.

## Intervention

### Description of Adherence Therapy

CAAT-PARK is a brief, cognitive-behavioural approach aimed at facilitating a process of shared decision making [29,48]. CAAT-PARK is rooted in the observation that a person's beliefs impact on treatment adherence. The central theory is that when people make shared choices with a professional they are more likely to continue with those choices because they are personally owned and meaningful [30]. Identification and amplification of the personally relevant benefits of treatment, modifying beliefs about medication and exploring ambivalence towards medication taking behaviour represent interrelated constructs that are central tenants of the therapy. CAAT-PARK is delivered in five phases that form the core of the therapy (Figure 3): *assessment, medication problem-solving, a medication timeline (looking back), exploring ambivalence, and discussing beliefs and concerns about medication*. Key therapy skills incorporate exchanging information, developing discrepancy between the patient's thoughts and behaviours about medication, socratic style questioning and working with resistance to discussing medication and treatment. The aim of CAAT-PARK is to achieve a mutual, informed decision about medication between the individual and therapist. A key concept is that where patients and therapists make choices about treatment mutually, adherence to that regimen will be enhanced [48,49].

**Figure 3 F3:**
[figure not shown]
**CAAT-PARK model**.

Participants allocated to CAAT-PARK will receive seven 30 minute sessions at weekly intervals. Assessment and problem solving will be delivered twice, making up seven sessions in total. Each weekly session will incorporate a separate theme, however, each session will be participant centred. Where a patient's carer has consented to the trial, the intervention will be delivered to the carer at the same time. Ten sessions over the course of the trial will be recorded to determine treatment fidelity against the CAAT-PARK manual [49].

### Treatment as Usual

Participants randomised to TAU will receive no additional information regarding medication adherence. Care will continue as usual according to routine practice. We will not provide any guidance to the clinical team as to the content of the usual care. Routinely usual care constitutes a clinic visit every 9-12 months to see the hospital consultant who is managing the patient's PD. Neurology specialist nurses may also see patients for routine follow-up between consultant clinics.

### Adverse Event Monitoring

Adverse events (AE) will be determined at each weekly visit and will commence from the point of randomisation up to week 12 follow-up. An AE checklist was developed following consensus views of the Trial Steering Committee (TSC) and medical specialists. AEs will be reported to the TSC and the participants' clinical team for appropriate action. All AEs will be addressed according to local Standard Operating Procedures (SOPs) for clinical trials of non-Investigational Medicinal Products (non-IMPs) developed in accordance with the Medicines for Human Use Regulations (2004) and the Department of Health's Research Governance Framework for Health and Social Care for identifying, recording, and reporting adverse events in clinical trials.

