### Ethical Considerations

Although we do not anticipate any risk to study participants, we acknowledge the small possibility that increased medication adherence in PD may lead to greater incidence of dyskinesia. Dyskinesia is a common motor complication resulting from dopaminergic therapy in PD and will therefore be monitored by the TSC. It is theoretically possible that greater medication adherence may trigger drug induced psychosis, a rare but important complication of dopaminergic therapy in PD, so this will also be monitored in all participants receiving CAAT-PARK for its potential development.

The trial protocol and all related documents were given a favourable ethical opinion by Cambridge Central NHS Research Ethics Committee (REC reference number: 11/EE/0179).

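### Adverse events are tied to weekly visits described only for CAAT-PARK, and psychosis monitoring is stated for that arm only, so the data could not support a between-arm safety comparison

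*Protocol article*

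**What the plan says.** All references are to the protocol article.

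- **Adverse Event Monitoring** fixes when events are sought: "Adverse events (AE) will be determined at each weekly visit and will commence from the point of randomisation up to week 12 follow-up". It names no arm. Events go to the Trial Steering Committee (TSC) and the participant's clinical team for action, using a checklist and local operating procedures that are not shown.
- **Intervention**, after Figure 3: "Participants allocated to CAAT-PARK will receive seven 30 minute sessions at weekly intervals".
- **Follow-up Measurements**: "For the control group receiving TAU, assessments will be at week seven and week twelve". For the other arm: "For the CAAT-PARK group, post intervention assessments will be at week seven or eight and then at week 12".
- **Treatment as Usual**: "Routinely usual care constitutes a clinic visit every 9-12 months to see the hospital consultant who is managing the patient's PD". Specialist nurses may also see patients between those visits.
- **Ethical Considerations** raises two possible harms of better adherence. On dyskinesia: "Dyskinesia is a common motor complication resulting from dopaminergic therapy in PD and will therefore be monitored by the TSC". On drug-induced psychosis: "so this will also be monitored in all participants receiving CAAT-PARK for its potential development".
- **Secondary outcomes** include MDS-UPDRS Part IV (motor complications). It is rated before randomisation and repeated on the common follow-up schedule.
- **Trial Objectives**, **Outcome Measures** and the **Analysis** section list no comparison of adverse events between arms.

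**The concern.** Someone who is asked more often reports more. If one arm is asked at home every week and the other at most twice, crude event counts will tend to look worse for the arm asked more often, even when the therapy does no harm.

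This matters here because the protocol itself says that raising adherence, which is the trial's aim, might bring on dyskinesia or psychosis. It also calls dyskinesia common under dopaminergic therapy, so background events can be expected in both arms. The TSC would see reports from CAAT-PARK without a control rate gathered in the same way. It could not readily separate a real effect from closer questioning, and events in TAU could go unrecorded.

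This is a matter of data collection, so no later analysis plan can recover events that were never asked about.

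**Working it through.** The plan gives no figure to reproduce. The check counts the contacts described, tests whether the sections fit together, and then illustrates what the imbalance could do.

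**1. Contacts after randomisation**

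| | CAAT-PARK | TAU |
|---|---|---|
| Weekly sessions | 7 | 0 described |
| Post-intervention assessment | week 7 or 8 | week 7 |
| Follow-up assessment | week 12 | week 12 |
| Total | 7 + 2 = 9, or 8 if session 7 and the assessment coincide | 2 |

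The ratio of contacts is 8/2 = 4.0 to 9/2 = 4.5. A consultant visit every 9 to 12 months will often not fall within a 12-week window, and nurse visits are only possible.

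**2. Do the sections fit together?**

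- *Between arms:* either TAU participants have weekly visits that are described nowhere, or events are sought on unequal schedules. The text needs reconciling in both cases.
- *Within CAAT-PARK:* seven weekly sessions end around week 7, yet collection at weekly visits is to continue to week 12. No weekly contact is described for weeks 8 to 11.
- *Psychosis:* the arm restriction is stated in words and needs no inference.

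**3. What unequal contact could do when true risk is equal**

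Assumptions, none of them from the document:

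- CAAT-PARK contacts fall at weeks 1 to 7 and 12 (8 contacts) and TAU contacts at weeks 7 and 12.
- The TAU contacts do include adverse event questions.
- The weekly risk *r* is constant and the same in both arms.
- An event is recorded only if it falls within the recall window before a contact.

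The ratio of expected recorded events is then (weeks covered in CAAT-PARK)/(weeks covered in TAU). The share of patients with at least one recorded event is 1 − (1 − r)^(weeks covered), shown for an assumed r = 2%.

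| Recall window | Weeks covered, CAAT-PARK | Weeks covered, TAU | Ratio | Share recorded at r = 2% |
|---|---|---|---|---|
| 1 week | 1–7, 12: 8 | 7, 12: 2 | 8/2 = 4.0 | 15% vs 4% |
| 2 weeks | 1–7, 11–12: 9 | 6–7, 11–12: 4 | 9/4 = 2.25 | 17% vs 8% |
| 4 weeks | 1–7, 9–12: 11 | 4–7, 9–12: 8 | 11/8 = 1.4 | 20% vs 15% |
| Whole interval since last contact, perfect recall | 12 | 7 + 5 = 12 | 1.0 | equal |

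For example, in the first row: 1 − 0.98^8 = 0.149 and 1 − 0.98^2 = 0.040. If the post-intervention assessment is a separate week-8 contact, the one-week row becomes 9/2 = 4.5.

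**4. After the fix**

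With the same contacts, checklist and look-back in both arms, the expected ratio under equal true risk and equal reporting is 1.0. No other figure in the document changes.

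**The case against.** There is a fair case on the other side, in five parts.

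- **No planned comparison is broken.** A reader might infer that the trial's safety analysis is invalid. The document does not support that, because it plans no such analysis. Adverse event data serve participant protection through the TSC and clinical team, and watching recipients of a new intervention more closely is defensible for that purpose. This stands. The defect is limited to what the data could support.
- **The lack of event collection in TAU is an inference.** A reader might infer that TAU participants are never asked. The monitoring section names no arm, nothing excludes questions at weeks 7 and 12, and the assessment figure, checklist and operating procedures are not shown. The sentence is loose even for CAAT-PARK. This lowers confidence in the inferred schedule, but it does not explain which weekly visits are meant or remove the express restriction on psychosis.
- **Dyskinesia is largely covered.** TSC monitoring of it is not limited to one arm, and MDS-UPDRS Part IV is repeated in both arms at nearly matched times. This stands, with the qualification in Study Limitations that follow-up outcomes are unblinded. It would be wrong to say that the trial cannot compare dyskinesia at all.
- **Psychosis is called rare.** With 46 per arm and an assumed 12-week risk of 1% to 2%, expected cases per arm are 46 × 0.01 = 0.46 to 46 × 0.02 = 0.92. Equal monitoring would not make a formal comparison informative. That is so, but a case in CAAT-PARK is still easier to interpret if TAU was asked the same question. The sentence also does not exempt TAU from general event recording.
- **A fourfold bias is a ceiling.** It needs each contact to capture only about one week. This stands, so a range must be given.

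**Conclusion.** The point holds in a limited form. As described, adverse events are sought at weekly visits that appear only in CAAT-PARK, and psychosis monitoring is stated for that arm alone. The weekly schedule does not match the 12-week collection window even there.

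No stated analysis is invalidated and the efficacy conclusions are untouched. What is lost is the ability to set adverse event or psychosis counts in one arm against the other, and a comparable control rate for the TSC.

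The contact imbalance is about 8 to 9 against 2. Its effect on recorded events under equal true risk runs from 1.0 to about 4.0. It cannot be narrowed without the recall window, and the bias, if any, would tend to count against CAAT-PARK. The range rests on the assumed contact weeks, a constant and equal weekly risk, and the reading that TAU has no weekly contact. The last is the only reading that fits the contacts described, but it is not stated. Reading the document as leaving TAU with no harm data, or as guaranteeing a fourfold distortion, goes beyond what it says.

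**What to change.** Reconcile Adverse Event Monitoring, the session schedule under Intervention, Follow-up Measurements and Ethical Considerations so that they describe one collection scheme:

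1. Give the existing checklist, including dyskinesia and psychosis items, to all randomised participants at the two shared assessments (week 7 or 8, and week 12), with the same look-back period. A fixed number of weeks is better than the time since randomisation, because the first assessment can fall a week later in CAAT-PARK.
2. Word the recording of psychosis for all randomised participants.
3. Base any between-arm summary of events only on those two time points, read alongside MDS-UPDRS Part IV.
4. List events elicited at weekly therapy sessions separately for CAAT-PARK, and state how events are collected after the sessions end.

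If the sponsor prefers to keep the present collection, the text should say that event counts are not comparable between arms.

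The cost is one short checklist added to two assessments that already take place, with no new visits. Unblinded reporting remains, and participants questioned weekly may recall more at the shared assessments. The change removes the unequal schedule but not those two sources of bias.
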